### Study parameters collected:

T0:

- Medical history: ASCVD; T2DM; intolerances to alirocumab, ezetimibe or statins
- LDL-c
- Statin use at baseline
- ezetimibe use at baseline

T4:

- Final statin use at T4
- LDL-c
- Development of statin intolerance
- If statin intolerant:
  - Which 3 statins are used
  - Recurrent intolerance?

T8:

- Final statin use at t8
- LDL-c

- Intolerance to Ezetimibe
- Which Alirocumab is started

T12:

- LDL-C

T52:

- LDL-c
- Statin use
- Alirocumab use
- Adherence
- MACE

Additional parameters:

- CHF, hypertension, age ( $\geq 75$  yr), diabetes, prior stroke, prior CABG, peripheral artery disease, eGFR  $< 60$ , smoking [15]
- SAE and AE at each consecutive step
- Optional: non-HDL, triglyceride, plasma levels at each consecutive step
- ASALT, ALAT, AF, Bilirubine, Creatinin kinase, GGT, LVEF, pregnancy, alteration in non-study medication.

### **Data handling conventions:**

The data is collected in electronic case report forms (castoredc.com). The data is exported in an Excel file and analysed using Python.

### **Data Handling Conventions For Patient Data**

Out of range data:

LDL-c  $< 0.5$  mmol/L and  $> 7.5$  mmol/L are double checked in the patients' medical record.

The following data will be considered as missing values in the calculation:

LDL-c  $> 20$  mmol/L

Missing data:

Missing values are handled using pairwise deletion. The case is excluded from the analysis if one or more data points needed for that particular calculation is missing.

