## Synopsis

The primary objective of the PENELOPE study is to assess the prevalence of unmet target LDL-C (1.8 mMol/L) despite a standardized stepwise high intensity lipid modifying therapy in patients with ASCVD and at very high risk for recurrent events.

Consecutive patients presenting with a type I (N)STEMI and a history of ASCVD and/or Diabetes mellitus II will be included. Prevalence will be determined of unmet target LDL-C (1.8 mMol/L) at each therapeutic step (Baseline, high intensity statin therapy (HIST) , HIST+ ezetimibe, HIST + ezetimibe + PCSK9-I), and after one year of therapy.

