## Primary Endpoint

prevalence of an LDL-C >1.8 mMol/L in a subgroup of very high risk patients, despite guideline based therapy with HIST and/or ezetimibe

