## Statistical analysis

Statistical analysis will be descriptive only. The study is intended nor powered to perform intergroup analysis.

The prevalence of the patients not reaching the target level at baseline will be calculated by dividing the proportion of patients with LDL-C  $> 1.8$  mMol/L at baseline by the total included patients.

For each consecutive step the net and the cumulative effect will be calculated. The net effect is the percentage of patients who reach the target (LDL-C  $\leq 1.8$  mMol/L) in the corresponding step. The cumulative effect is the percentage of all patients who reach the target (LDL-C  $\leq 1.8$  mMol/L) in the previous and the current steps. The labelling of the groups and the calculation of the net and cumulative effect are shown in figure 2.

In patients with Ezetimibe monotherapy because of a statin intolerance the net effect is calculated in the same manner as the patients with HIST end ezetimibe. The calculations will be performed for the total population and separately for patients with a history of ASCVD and DMII.

The results of the calculations will be presented in table 3.

The therapy during the first 12 weeks and the changes at one year follow-up will be presented in figure 3.

The cumulative effect in the first 12 weeks and at one year follow-up will be presented in figure 4.

The prevalence of drug-related adverse events and discontinuation rate of the lipid modifying drugs for the study population and subgroups (men and women,  $>70y$  and  $\leq 70y$ ) will be presented in a table. The intergroup analysis is performed using the Chi-squared test.

Prevalence of MACE is calculated as follows :  $\frac{\text{Patients with MACE at T52}}{\text{Total patients at T52}}$  The same calculation will be used for patients with decreased adherence for each treatment group (HIST, HIST+ezetimibe, HIST + Ezetimibe + PCSK-9i) and will be presented in table 3.

In the above mentioned analysis an LCL-c threshold of 1.8 mmol/l is used, the same analysis will be carried out using an LDL-c threshold of 1.4 mmol/L.

The percentage of patients with an LDL  $>1.8$  mmol/L and  $\leq 2.6$  mmol/L where a treatment with Alirocumab is started, will be calculated as follows:

$$\frac{\text{Patients with an LDL } > 1.8 \text{ mMol/L } \leq 2.6 \text{ mMol/L Alirocumab with}}{\text{Patients with an LDL } > 1.8 \text{ mMol/L } \leq 2.6 \text{ mMol/L on T8}}$$

[figure not shown]

Figure 2 Statistical analysis

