On the left side: Different groups are labelled (A,B,C,...) based on the LDL-value and the different stages/steps.  
On the right side: The calculation of the net (Ntx) and cumulative (Ctx) effect for each step (T4,T8,T12) effect are shown. The net effect is the percentage of patients who reach the target (LDL-C ≤ 1.8 mMol/L) in the corresponding step. The cumulative effect is the percentage of all patients who reach the target (LDL-C ≤ 1.8 mMol/L) in the previous and the current steps  
For T0 the of calculation of the prevalence (Pt0) of patients with an LDL ≤ 1.8mMol/L is shown.

Table 3 Summary of the collected data

| Net effect of each consecutive step                               |                 |                 |                  |                            |
|-------------------------------------------------------------------|-----------------|-----------------|------------------|----------------------------|
|                                                                   | Pt 0 | Nt 4 | Nt 8  | Nt 12           |
| LDL≤ 1.8 mMol/L                                                   | n (%)           | n (%)           | n (%)            | n (%)                      |
| Cumulative effect of the consecutive steps                        |                 |                 |                  |                            |
|                                                                   | Pt 0 | Ct 4 | Ct 8  | Ct 12           |
| LDL≤ 1.8 mMol/L                                                   | n (%)           | n (%)           | n (%)            | n (%)                      |
| Prevalence of patients not reaching target at the different steps |                 |                 |                  |                            |
|                                                                   | T 0  | T 4  | T 8   | T 12            |
| LDL> 1.8 mMol/L                                                   | n (%)           | n (%)           | n (%)            | n (%)                      |
| One year follow up                                                |                 |                 |                  |                            |

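### Under the cumulative, all-patient definition, pairwise deletion for a missing T8 or T12 LDL-C drops only patients not yet at target, so unmet LDL-C is expected to be understated

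*SAP*

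**What the plan says.** **Missing data.** SAP, Data Handling Conventions For Patient Data: "Missing values are handled using pairwise deletion", followed by "The case is excluded from the analysis if one or more data points needed for that particular calculation is missing". LDL-C above 20 mmol/L is also set to missing. No other missing-data method and no sensitivity analysis for missing values is stated.

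**Stepwise estimates.** The Synopsis says "Prevalence will be determined of unmet target LDL-C (1.8 mMol/L) at each therapeutic step", the steps being baseline, high-intensity statin (HIST), HIST plus ezetimibe, and the addition of a PCSK9 inhibitor. Statistical analysis defines two summaries per step. For the net effect: "The net effect is the percentage of patients who reach the target (LDL-C ≤ 1.8 mMol/L) in the corresponding step". For the cumulative effect: "The cumulative effect is the percentage of all patients who reach the target (LDL-C ≤ 1.8 mMol/L) in the previous and the current steps". Table 3 reports both, together with the prevalence not at target at T0, T4, T8 and T12.

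**Primary endpoint.** It is the prevalence of LDL-C above 1.8 mmol/L "in a subgroup of very high risk patients, despite guideline based therapy with HIST and/or ezetimibe". No formula for its denominator appears in the text. The group labels and formulas are assigned to Figure 2, which is not available in the copy reviewed.

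**Precision.** Sample size calculation assumes a prevalence of 20% and asks for a 95% confidence interval with a half-width of 2.5 points. This gives 983 patients, rounded up to 1000.

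**The concern.** Pairwise deletion is often treated as harmless when values are missing at random. In a stepwise cumulative summary it need not be. Whether a patient has a value that the calculation needs depends on how that patient did at the previous step. Someone at target at T4 is already classified as a success for T8; someone above target at T4 is not classified until a T8 value arrives. Deletion for a missing T8 value therefore falls entirely on T4 failures, who are more likely than the average patient to be above target at T8.

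The figure at stake is the primary prevalence of a study that the SAP describes as descriptive, so the estimate and its interval are the main result. A larger sample narrows the interval but does not remove a bias of this kind. The same mechanism would carry into the T12 figure and, in the opposite direction, into the cumulative effect.

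**Working it through.** **1. The plan's own figure.** n = Z²p(1−p)/d² = 1.96² × 0.20 × 0.80 / 0.025² = 983.4, which agrees with the stated 983. At n = 1000 the half-width is 1.96 × √(0.16/1000) = 2.48 points.

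**2. Which denominator the sizing implies.** The stated precision needs about 1000 patients in the denominator of the primary prevalence. If only an assumed 40% of 1000 (400 patients) entered the ezetimibe step and formed the denominator, the half-width would be 1.96 × √(0.16/400) = 3.9 points at a prevalence of 20%, or 1.96 × √(0.25/400) = 4.9 points at 50%. The sizing therefore fits an all-patient denominator better than a step-specific one.

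**3. Inputs for the bias.**
- p = 0.20, true unmet prevalence at T8 among all patients (the SAP's planning value).
- f = share above target at T4. Not in the SAP; 0.40 assumed, varied below.
- q = p/f = share of T4 failures still above target at T8 = 0.20/0.40 = 0.50.
- m = share of T4 failures without a T8 value, missing at random among them. Not in the SAP; varied.

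**4. Estimate under deletion.** Of all patients, a fraction f·m is deleted, and f(1−m)q remain and are seen to be above target:

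p_obs = f(1−m)q / (1 − f·m)

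| m | Calculation | Estimate | Bias (points) |
|---|---|---|---|
| 5% | 0.19/0.98 | 19.4% | −0.6 |
| 10% | 0.18/0.96 | 18.75% | −1.25 |
| 20% | 0.16/0.92 | 17.4% | −2.6 |

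The bias reaches 2.5 points when 0.20(1−m)/(1−0.40m) = 0.175, that is m = 0.025/0.13, or about 19%.

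**5. Sensitivity to f.** At m = 10% the bias runs from −1.5 points (f = 0.25) to −0.4 points (f = 0.80). It is zero at f = 1, where every patient needs a T8 value.

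**6. Sensitivity to who is missing.** If deleted patients are above target at rate r, then p_obs = (p − f·m·r)/(1 − f·m). At f = 0.40 and m = 10% the bias is +0.8 points for r = 0, 0 for r = 20%, −1.25 for r = 50% and −3.3 for r = 100%. The estimate is too low exactly when r exceeds p. Under random missingness within the step r = p/f, which exceeds p whenever f is below 1.

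**7. Step product on the same data.** Take 1000 patients, 400 above target at T4, 80 of those without a T8 value (m = 20%), and 160 of the remaining 320 above target. Deletion gives 160/920 = 17.4%, and a cumulative effect of 82.6% instead of 80%. The product gives 400/1000 × 160/320 = 20.0%.

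**The case against.** The strongest reply is that the mechanism rests on a reading that the visible text does not fully settle. Figure 2 holds the formulas and cannot be seen. The primary endpoint refers to a subgroup, not to all patients. If its denominator is the patients who entered the ezetimibe step, random missingness within that step causes no bias. LDL-C is also listed for collection at T4, T8, T12 and T52 without restriction to patients above target, so early achievers might be required to supply later values and could then be deleted too. And the size depends on two assumed inputs: at 5% missing the shift is only 0.6 points.

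Most of this stands as a limit on certainty. The collection list weakens the point least, because the deletion rule turns on whether a value is needed for the calculation, not on whether it is collected; the cumulative definition needs none from an early achiever. The sizing supports the all-patient denominator but does not prove it.

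Three stronger readings are tempting and are not supported:
- **That deletion always removes only earlier failures.** This holds for missing T8 or T12 values under the cumulative definition. A missing T0 or T4 value can remove patients whose status at that step is simply unknown.
- **That a missing baseline value counts as at target**, because the baseline formula divides "by the total included patients". The deletion rule can be read as already governing that formula, in which case the patient leaves numerator and denominator together.
- **That the one-year figure has the same defect.** The T52 block of Table 3 is a cross-sectional count. Patients lost by then raise the ordinary question of informative dropout, not this stepwise mechanism.

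**Conclusion.** The point holds conditionally. On the cumulative, all-patient definition, which the sample size supports for the primary prevalence, the stated deletion rule is expected to understate unmet LDL-C at T8 and T12. With 40% above target at T4 and a true 20% at T8, the shift is about 0.6 to 2.6 points for 5% to 20% missing among T4 failures. It exceeds the planned 2.5-point margin only above about 19% missing.

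A reader might infer that the primary result is certain to be biased downward. The SAP does not support that: the bias vanishes with a step-specific denominator and random missingness within the step, and it reverses if the deleted patients are above target less often than the whole cohort. The reversal would be an unusual pattern, since at these inputs it needs a rate below 20% in a group averaging 50%. The matter should be fixed, with moderate confidence. The sample size calculation itself is not affected.

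**What to change.** - State the primary denominator explicitly as all included patients with a usable T0/T4 classification, and say that patients at target at an earlier step are carried forward as at target.
- For the primary and cumulative figures, replace pairwise deletion by the step product P(>1.8 at T4) × P(>1.8 at T8 | >1.8 at T4), with a further factor for T12. Each factor uses the patients observed at that step. The product is unbiased if missingness is random within the step. If patients at target at T0 are likewise carried forward without a T4 value, start the product at T0 for the same reason.
- Add a sensitivity analysis that counts a missing value after a failed step as not at target. At the inputs above with m = 10% it would give 0.18 + 0.04 = 22%, a conservative upper figure.
- Report the number missing at each step next to the Table 3 entries.

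The cost is a few sentences in the SAP, a few lines of analysis code and slightly more output. The reported prevalence may be somewhat less favourable.
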